# Observation on clinical effect of Huoxue-Jiangtang decoction formula granules in treating prediabetes: a randomized prospective placebo-controlled double-blind trial protocol

**DOI:** 10.1186/s12906-022-03755-2

**Published:** 2022-10-19

**Keywords:** Prediabetes, Huoxue Jiangtang formula, Randomized controlled trial, Traditional Chinese medicine

## Abstract

**Background:**

Prediabetes is a hypermetabolic syndrome with blood sugar levels falling between the normal and diabetes. People with prediabetes have a significantly increased chances of developing diabetes, cardiovascular and cerebrovascular diseases, tumors, dementia, and other diseases in the future when compared to the healthy population. However, prediabetes is mainly treated based on lifestyle intervention, currently without targeted drug treatment plan. Traditional Chinese medicine (TCM), which has a longstanding experience, has been shown in clinical studies to be effective for the treatment of diabetes and its related complications. Furthermore, different dosage forms such as decoction and granule have developed gradually in clinical application. Preliminary studies have found that Huoxue-Jangtang Decoction (HJD), with good hypoglycemic and lipid-regulating effects, is potentially one of the complementary and alternative treatments for prediabetes. Therefore, this project intends to perform a prospective clinical study to observe the clinical effectiveness of HJD on prediabetes and the consistency of the efficacy of formula granules and the elixation.

**Methods:**

This is a prospective, randomized, double-blind, and placebo-controlled clinical trial. A total of 183 participants are randomly assigned to HJD Formula Granules plus lifestyle intervention, HJD Elixation plus lifestyle intervention, and placebo plus lifestyle intervention. All subjects undergo 1 day of screening before participating in the study, followed by 84 days of drug intervention and observation. During and after treatment, the main outcome measures include fasting blood glucose and 2-hour postprandial blood glucose.

**Discussion:**

This research attempts to verify the clinical efficacy and possible mechanism of HJD in the treatment of prediabetes, and prove the consistency of HJD Formula Granules with HJD Elixation. This study also aims to provide a treatment that is both effective and safe for prediabetic patients.

**Trial registration:**

ClinicalTrials.gov Identifier: ChiCTR2200060813, Registered 12 June 2022.

## Background

Prediabetes, considered to be an important clinical stage of diabetes, is a hypermetabolic syndrome with blood sugar levels falling between the normal and diabetes. In the past 40 years, the lifestyle and diet structure of Chinese people have undergone great changes due to a rapidly expanding economy. A lack of exercise and high-calorie diet have significantly increased the proportion of prediabetic and diabetic patients in the Chinese population. The epidemiological statistics in China in 2017 show that 35.2% of the population have pre-diabetes, and 11.2% of the population have diabetes. However, only 4.0% of them have been clearly diagnosed just 49.2% of which have received adequate treatment [1, 2].

When the prediabetic patients do not receive timely diagnosis and treatment, about 5–10% of them will rapidly progress to the stage of diabetes, and the rest will gradually develop diabetes over the next 5 years. In the meantime, the incidence and severity of diseases such as coronary artery disease, heart failure, hypertension and retinopathy in patients with prediabetes are aggravated with more obvious blood glucose fluctuation, thus seriously affecting their quality of life [3–6]. As a result, timely diagnosis and intervention for diabetics can postpone the progression of prediabetes to diabetes and lower the risk of related complications, which is critical for both society and patients.

Fat, a strong temptation for human beings, provides necessary calories for normal physiological activities as one of the important food types. In a meta-analysis of dietary behavior, it is found that Chinese patients with type 2 diabetes generally preferred fat, oil, sweets and meat [7]. Long-term high-fat food intake can reduce an individual’s sensitivity to fat, leading to excessive fat intake, weight gain and insulin resistance [8]. Several studies have also discovered that people who consume a high-fat diet are at a markedly increased risk of experiencing prediabetes [9–12]. For this reason, the American Diabetes Association (ADA) recommends that diabetes and prediabetes patients should adjust their lifestyle and choose whole grains and fiber over high-fat, high-calorie and high-sweetness food to reduce the risks associated with diet [13].

The Diabetes Prevention Program has shown that lifestyle intervention can decrease the occurrence of prediabetes conversion by 58% [14]. In addition, lifestyle interventions require no additional financial costs or time requirements, so patients can do corresponding exercise in their free time, which remains the main measure and first choice for the prevention and treatment of prediabetes [15–17]. However, it’s not easy for some people to change a long-standing diet or lifestyle, and the lack of a consistently effective lifestyle intervention is also less effective in prediabetes. Although clinical researches have found that metformin, acarbose, orlistat and other drugs can prevent prediabetes from developing into diabetes by reducing body weight, improving glucose metabolism and other mechanisms, etc., there is still no consensus [18–21].

Traditional Chinese medicine (TCM) has been used to treat a wide range of diseases in China for thousands of years. In the process of application, granules, powder and other new formulations have been developed, however, formula granules and elixation are the two most widely used dosage forms. Previous research has found that TCM therapies can noticeably and securely improve the symptoms and clinical indicators of diabetes and prediabetes patients, so it appears to be a potential complementary therapy for prediabetes [22, 23].

In a meta-analysis of 26 randomized controlled trials, TCM treatment delayed the development of impaired glucose tolerance to diabetes and increased the likelihood of normalizing blood glucose in diabetics compared to the control groups. Compared with lifestyle intervention alone or drug therapy alone, TCM therapy had a more significant effect on improving the symptoms and indicators of prediabetes, diabetes and related complications [24].

Huoxue-Jangtang Decoction (HJD) is the precompounded prescription order of the Endocrinology Department of Shenzhen Traditional Chinese Medicine Hospital (Shenzhen TCM Hospital). Our earlier studies have shown that HJD has the effects of lowering glucose and controlling lipid, improving insulin resistance and reducing oxidative stress reaction, etc. It has been clinically applied to the treatment of T2DM, diabetic nephropathy, diabetic peripheral vascular disease and other diseases, with good therapeutic effect and safety [25–27].

However, research on the efficacy and clinical adverse reactions of HJD in prediabetic patients is still lacking. In addition, while the decoction is effective, the preparation process is tedious and time-consuming. Granules can be taken after mixed with warm boiled water, which can bring great convenience to patients, but there still lack persuasive evidence of efficacy consistency between the two dosage forms. For this reason, we designed this study protocol to evaluate the effectiveness and tolerability of HJD in the prevention and treatment of prediabetes. In addition, it is also aimed to verify the consistency between the Elixation of Huoxue-Jiangtang Decoction (HJD Elixation) and the Formula Granules of Huoxue-Jiangtang Decoction (HJD Formula Granules).

## Methods/design

### Design and setting

This study is a prospective, randomized, double-blind, placebo-controlled trial that has been registered with the China clinical trials registry (registration number: ChiCTR2200060813). All the documents including study protocol, informed consent, and Case Report Forms (CRF) meet the requirement of the Helsinki declaration, and have been reviewed by academic committee and ethics committee of Shenzhen TCM Hospital. This protocol was compiled in line with the SPIRIT 2013 (Table 1).

**Table 1 Tab1:**
[figure not shown]
A standard protocol items: recommendation for interventions for trials (SPIRIT)

### Participants

#### Sample size

Sample size is calculated by PASS 15.0 software, with the significance level of 0.05. A total of 189 cases (63 cases in each group) are required to detect inter-group differences in 2.6 mmol/L postprandial 2 h glucose, with a statistical power of 90%. The sample size calculation assumes a standard deviation of 2.0 mmol/L and a shedding rate of 20%.

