### Statistical analysis

Primary, secondary, exploratory end points and safety assessments will be analyzed when the last patient completes the follow-up or drops out of the study. Analyses of clinical data will be performed by the principal investigator including subjects’ demographic, clinical, and laboratory data.

Continuous variables are used to evaluate the number of cases, mean, standard deviation, median, minimum, and maximum for demographic data and other baseline eigenvalues. Frequency and composition ratio are calculated using count and grade data. Descriptive results invole inferential statistical results (*p*-values).

For the analyses of laboratory data and clinical efficacy of drugs, chi-square test or Fisher’s exact test are used for counting data, while ANOVA and T test are used for measurement data. The grade data is analyzed by Ridit and CMH. The ratio or percentage of counting data is expressed, and the measurement data is expressed as mean ± standard deviation. All statistical tests are conducted by two-sided tests, with *P* < 0.05 indicating statistical significance. Multiple imputation will be used for missing data.

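### The stated sample-size inputs give about 17–18 enrolled per group, not 63, so the difference, the SD or the N is misstated

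*Protocol article*

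**What the plan says.** The Sample size section of the protocol article gives a full set of inputs and a result. It begins "Sample size is calculated by PASS 15.0 software, with the significance level of 0.05" and then states that "A total of 189 cases (63 cases in each group) are required to detect inter-group differences in 2.6 mmol/L postprandial 2 h glucose", the power being 90%. It ends: "The sample size calculation assumes a standard deviation of 2.0 mmol/L and a shedding rate of 20"%.

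The Randomization section repeats 63 per group in three groups at 1:1:1. The Statistical analysis section says "All statistical tests are conducted by two-sided tests" and names ANOVA and t tests for measurement data. The Methods part of the abstract gives a different total, 183. The article states no multiplicity adjustment and no equivalence or non-inferiority margin that could raise the requirement.

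**The concern.** A difference of 2.6 mmol/L against an SD of 2.0 mmol/L is a standardised difference of 1.3. An effect that large needs only small groups at 90% power, so 63 per group is hard to reconcile with it even after allowing for 20% loss.

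This sentence is the only justification the article gives for the number of patients, and 2-hour glucose is the only outcome used for sizing. If the difference is misstated, readers will judge the primary result against the wrong target. If the SD is misstated, they will expect about twice the precision that the design assumes. If both inputs are as intended, the trial enrols several times the number they require, with no stated reason.

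**Working it through.** **Inputs.** Difference 2.6 mmol/L, SD 2.0 mmol/L, significance level 0.05, power 90%, loss 20%, stated result 63 per group (all from Sample size). Two-sided testing comes from Statistical analysis, because the Sample size section does not say. The normal quantiles are 1.960 and 1.2816.

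**1. Attempt to reproduce 63 from the stated inputs.** For a comparison of two means,

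n = 2 × (1.960 + 1.2816)² × (SD / difference)²

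= 2 × 10.508 × (2.0 / 2.6)² = 12.4, so 13 evaluable per group.

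- Allowing for 20% loss: 13 / 0.8 = 16.25, so 17 enrolled.
- The exact two-sample t test (noncentral t) gives 14; 14 / 0.8 = 17.5, so 18 enrolled.
- Total for three groups: 3 × 17 = 51 to 3 × 18 = 54, against 189.
- Ratio: 63 / 18 = 3.5 and 63 / 17 = 3.7.

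**2. Other ways the calculation could have been set up**, with 2.6 kept and SD 2.0 in every row but the last:

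| Set-up | Evaluable per group | Enrolled per group |
|---|---|---|
| One-sided 0.05 | 11 | 14 |
| Three-group ANOVA, two means equal and the third 2.6 away | 13 | 17 |
| Three-group ANOVA, one mean midway, range 2.6 | 17 | 22 |
| Bonferroni for 2 comparisons (normal; t) | 15; 17 | 19; 22 |
| Bonferroni for 3 comparisons (normal; t) | 16; 18 | 20; 23 |
| Equivalence (two one-sided tests), margin 2.6 | 13–16 | 17–20 |
| SD multiplied by √2 (normal; t) | 25; 26 | 32; 33 |

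None comes near 63.

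**3. What the stated N can detect.** 63 × 0.8 = 50.4, so about 50 evaluable per group. With SD 2.0:

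- Power at 2.6 mmol/L (noncentral t) is 0.999996.
- The difference detectable with 90% power is 2.0 × √(2/50) × 3.2416 = 1.30 mmol/L by normal approximation. By the exact t test, power at 1.3 is 89.6%.
- For a three-group ANOVA, the maximum difference detectable with 90% power is 1.24 (two means equal) to 1.44 mmol/L (one mean midway).

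**4. Which inputs would give 63.** The formula depends only on difference / SD. A ratio of 0.65 gives

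2 × 10.508 / 0.65² = 49.7, so 50; 50 / 0.8 = 62.5, so 63 enrolled and 189 in total.

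Both 1.3 / 2.0 and 2.6 / 4.0 equal 0.65. The exact t test gives 51; 51 / 0.8 = 63.75, so 64 enrolled and 192 in total. The match to 63 is therefore exact under the normal approximation and one patient per group out under the t test.

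**The case against.** The strongest reply is that the discrepancy is on the safe side. If 2.6 and 2.0 are both right, power is far above 90%, no conclusion is put at risk, and the matter is one of reporting. That is true under that reading. It does not rescue the sentence, which says that 189 are needed for 90% power, and the article cannot show that this reading is the right one.

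A second reply is that another test or an adjustment may lie behind 63. The variants tried above reach at most 33 enrolled per group, and the article mentions nothing that would go further.

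A reader might infer more than the article supports, in three ways:

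- **That the target was really 1.3 mmol/L and 2.6 is a factor-of-two error.** The fit at 1.3 is suggestive, but 2.6 with SD 4.0 fits equally well, and the N itself could be wrong. The exact match also relies on the normal approximation. With a three-group ANOVA at a maximum difference of 1.3, the requirement is 46–61 evaluable, or 58–77 enrolled.
- **That the trial is underpowered.** This would require pairing SD 4.0 with a difference of 1.3, which combines two rival corrections. If 4.0 was the intended SD, the difference remains 2.6 and power is about 90%.
- **That 2.6 mmol/L is implausible because it covers most of the 7.8 to 11.1 mmol/L eligibility range.** The Inclusion criteria admit patients on fasting glucose and/or 2-hour glucose, so that range does not bound 2-hour values for everyone enrolled. Nor does it bound follow-up values.

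**Conclusion.** The sentence is wrong as written: its inputs and its N do not agree. The stated 63 per group compares with 17–18 under a two-sided two-group comparison and 17–22 under a three-group ANOVA, all after 20% loss. This assumes a parallel-group comparison of means with a common SD and loss handled by dividing by 0.8. One-sided testing would widen the gap. The adjusted and equivalence variants narrow it but leave it large.

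If the SD is 2.0, the trial has about 90% power for a two-group difference of about 1.3 mmol/L, half the stated figure. That statement is conditional on the SD. What is established is the inconsistency, not which of difference, SD or N caused it. It should be corrected because it is the only stated basis for the size of the trial.

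**What to change.** Re-run the PASS calculation and correct whichever of the difference, the SD or the N is wrong. In the same paragraph:

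- name the comparison and the test it refers to, since the article speaks only of differences between groups;
- say whether the calculation is two-sided;
- restate the detectable difference and the power at about 50 evaluable per group;
- reconcile 189 with the 183 in the abstract (61 per group), which the stated inputs do not reproduce either.

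If the difference or the SD is the misstated input, the correction is to that paragraph and enrolment need not change. If both are as intended, the sponsor should restate the power or give another basis for 189. The cost is one re-run calculation and a few corrected sentences.

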#### Recruitment

Subjects will be recruited from the inpatients or outpatients in the Endocrinology Department of Shenzhen TCM Hospital as well as local communities through recruitment advertisements or online promotion. The applicants and main members of the department have been well trained, with rich experience in clinical and experimental research. The Endocrinology Department of Shenzhen TCM Hospital has undertaken multi-stage clinical and basic research projects, and advanced experimental equipment as well as abundant outpatients and inpatients, which jointly ensure the source of patients, technical force and research conditions required by this project. Recruitment was carried out on June 1, 2022, and is supposed to be completed on January 31, 2024.

#### Patient screening

Prior to the trial, potential subjects will undergo screening at Shenzhen TCM Hospital in accordance with the criteria to determine whether they are eligible for the study. At first, doctors will introduce the study to him/her in as much detail as possible, and carefully answer the doubts of subjects and their families. It is critical that the subjects comprehend the purpose, procedure and duration of the study, as well as the benefits, risks and discomfort that may appear in the course of the research (as shown in Fig. 1).

**Fig. 1 Fig1:**
[figure not shown]
Study flowchart. Members with prediabetes will be enrolled and allocated randomly to one of three groups. All subjects will accept 1 day of screening, and 84 days of intervention and observation. The data is gathered to verify the clinical effectiveness and possible mechanism of Huoxue-Jangtang Decoction (HJD) in the treatment of prediabetes, and to prove the consistency of HJD Formula Granules with HJD Elixation

#### Inclusion criteria

Meet the diagnosis of “prediabetes”, namely, the criteria of “impaired fasting glucose” and “impaired glucose tolerance” in the classification of glucose metabolism state proposed by WHO in 1999 [28]. Which means that fasting glucose ≥6.1 mmol/L, < 7.0 mmol/L and/or OGTT 2-hour glucose ≥7.8 mmol/L, < 11.1 mmol/L.≥18 years old and < 70 years old.HBA1c ≤6.5%.Patients who have not participated in any interventional clinical study or clinical trial in the past 3 months.Patients who are able and willing to sign written informed consent and complete the study.

#### Exclusion criteria

Diabetics with clear diagnosis.Women during pregnancy and lactation.Patients with chronic kidney disease (eGFR< 60 mL/min/1.73m^2^ and/or serum creatinine > 133 μmol/L), severe liver dysfunction (any liver enzyme > 3 upper limit of normal, abnormal coagulation function or bilirubin), severe cardiac dysfunction (such as NYHA III or above heart failure, myocardial infarction, and arrhythmia), acute stage of cerebrovascular disease, or malignant diseases that are being treated or have not been fully alleviated or cured.Patients using high-dose probiotics (daily intake >108cFU) in the past 6 months.Patients using glucocorticoids, cytokines that can stimulate the body’s immune system, methotrexate and other immunosuppressants in the past 6 months.Patients systematically using antibiotics in the past 3 months.Patients using local antibiotics in oral cavity within 7 days (such as toothpaste and mouthwash containing antibiotics).Patients with an irregular diet in the past 3 months (the same meal time interval of more than 2 hours).Patients with untreated oral abscess.Patients with oral fungal infection.Patients with oral precancerous lesions or oral cancers.Patients with chronic periodontal diseases requiring long-term treatment.Patients allergic to any of the ingredients in linoleic solution.Persons not suitable for this project according to the researcher because of mental, psychological factors, etc.

### Randomization

Random number tables are provided by statistical professionals and generated by DAS software. The preparation of drug documentation and emergency correspondence is completed by personnel not involved in the clinical trial. Once subjects are recruited in the study, they will be randomly allocated into three groups at a 1:1:1 ratio, namely HJD Formula Granules group (*n* = 63), HJD Elixation group (*n* = 63) and placebo group (*n* = 63). During the trial, drugs will be distributed based on the time sequence of patients’ inclusion for observation and drug number. Drugs shall not be selected, and the drug number will remain unchanged throughout the trial.

### Blinding

This is a double-blind trial in which all the staff, investigators, sponsors and statisticians are blinded. The test drug and placebo are accompanied by an emergency letter with corresponding number, which are kept by the principal investigator. In the serious adverse events, or in need for emergency treatment, the investigator will report to the supervisor and the principal investigator and decide whether to open the emergency letter. The over 20% of opening rate in blind records leakage or emergency letter indicates test failure. After case collection is completed, the database is established and the data is locked, unblinding measures will be performed.

### Withdrawal criteria and management

Medication will be adjusted or terminated if any of the following conditions occur.

1. Severe adverse events related to abnormal blood glucose, such as diabetic ketosis, and hyperosmolar hyperglycemic state.

2. The occurrence of other serious cardiac, cerebral and renal vascular diseases during the test.

3. Severe gastrointestinal reactions.

4. The subjects deviate significantly from test requirements or want to withdraw from the study.

5. Investigators conclude that the subjects are no longer fit for participating in the study.

### Intervention

The main intervention measures include oral HJD Formula Granules, HJD Elixation or placebo in addition to daily lifestyle intervention. The individual personnel will package and label the investigational drug and placebo in accordance with random-number tables and drug blinds. All drugs are concealed in uniform packages with the same label and a 28-day supply. At each visit, the researchers will ask the patient about their medication and count the remaining dose to improve their compliance. Besides, any drug with a clear hypoglycemic effect shall not be used. Previous studies have proved that HJD has the effects of regulating glucose and lipid metabolism, improving inflammation and oxidative stress state, and improving insulin resistance, with good therapeutic effects on type 2 diabetes, metabolic syndrome, and diabetic nephropathy, etc. [25, 29, 30] The dosage of HJD Formula Granules and HJD Elixation is determined by the long-term clinical application experience of our hospital.

The subjects will also be instructed according to the prediabetic lifestyle intervention program contained in *Guideline for the Prevention and Treatment of Type 2 Diabetes Mellitus in China (2020 edition)* [31]. Generally speaking, it mainly includes but is not limited to diet control, exercise and health education, etc. [31]

